#### **Subject Withdrawal/ Withdrawal of Consent**

Subjects can withdraw from the study at any point and this will not be held against them. They will be informed during the consent process of this and will be asked to contact the research team so that the investigator can withdraw them from the study. If a subject should withdraw, the data and samples collected will be destroyed, unless they have already been analyzed or processed or coded.

## **9. Statistical Consideration and Data Analysis**

Power-calculation: In order to keep the total number of patients small we will match the patients according to age, co-morbidities inhaled oxygen fraction and we regard this investigation as a feasibility study. Therefore, the sample size calculation based on the assumption of an effect size (change in PaO2) of 1.5 SDS in the primary endpoint (PaO2), an intended power of 80%, an alpha error of 5% and an equal sample ratio results in n=7 patients needed to treat. However, to compensate for dropouts we will include 10 patients in each group, which means in total 20 patients.

Data analysis: Categorical data will be presented as number and percentage, while interval data will be presented by median and interquartile range (IQR). Normally distributed data will be analyzed by using two-tailed unpaired Students t-test. Continuous variables with skewed distribution will be analyzed using Mann-Whitney U testing and dichotomous variables by means of Fisher's exact test. A p-value <0.05 is considered significant. All data analyses will be done using SPSS version v26 (IBM Corp, Armonk NY, USA). Graphs will be constructed using GraphPad Prism (GraphPad Prism version 5.0a for Windows, GraphPad Software, San Diego CA, USA).

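### Seven patients per group give 73%, not 80%, power for the two-tailed t-test that Protocol section 9 names; the 10 enrolled are adequate but leave a dropout reserve of 1 to 2 per group, not 3

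*Protocol*

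**What the plan says.** Everything needed stands in Protocol section 9 (Statistical Consideration and Data Analysis).

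- **Effect:** "an effect size (change in PaO 2 ) of 1.5 SDS in the primary endpoint".
- **Power, alpha, ratio and result:** "an intended power of 80%, an alpha error of 5% and an equal sample ratio results in n=7 patients needed to treat". The sentence does not say whether 7 is per group or in total. The next sentence raises it to 10 per group, so per group is the only sensible reading.
- **Dropouts:** "However, to compensate for dropouts we will include 10 patients in each group", 20 in total. No dropout rate is given.
- **Analysis:** a "two-tailed unpaired Students t-test" for normally distributed data, with significance at p<0.05. For the other case, "Continuous variables with skewed distribution will be analyzed using Mann-Whitney U testing".

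The power calculation itself names neither the test nor its sidedness. Section 9 also says that patients will be matched on age, co-morbidities and inhaled oxygen fraction, and it calls the trial a feasibility study.

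**The concern.** A sample size belongs to a particular test. Section 9 states an effect, a power and an alpha, derives 7 from them, and a few lines later names a test for which 7 per group does not deliver that power.

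The 7 also carries weight beyond its own sentence, because it sets the size of the dropout allowance. Moving from 7 to 10 per group tells the team that three patients in each group can be lost with the design still at 80%. Losses are foreseeable from the protocol itself. Under section 6 a patient's study period ends early on deterioration needing prone positioning or ECMO. Under Subject Withdrawal in section 8, a withdrawn patient's data are destroyed unless already analysed, processed or coded. A team that finished with 7 evaluable patients per group would believe that it had the planned power, when its chance of missing the assumed effect would be about 27% (100 − 73.1) rather than 20%.

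**Working it through.** **Inputs (all Protocol section 9).** Standardised effect d = 1.5; two-sided alpha 0.05 (sidedness taken from the named test); power 0.80; 1:1 allocation; unpaired t-test.

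**1. Reproducing the stated 7.** The large-sample normal formula is

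n per group = 2 × (z₀.₉₇₅ + z₀.₈₀)² / d² = 2 × (1.96 + 0.8416)² / 1.5² = 6.98, rounded up to 7.

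By the same approximation, power at 7 is 80.1%. So the 7 is a correct evaluation of that formula. The formula treats the SD as known, which a t-test with 7 per group does not.

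**2. Other routes to 7.**

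- One-sided normal formula at 5%: 5.50, rounded up to 6.
- One-sided t-test at 5%: 78.0% at 6 and 84.1% at 7, so this also gives 7. Section 9 says two-tailed.
- Two-sided paired t-test with 1.5 SD of the within-pair differences: 83.3% at 6 pairs, so 6 rather than 7. Section 9 says unpaired.

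**3. Power of the named test.** For group sizes n₁ and n₂, use the noncentral t distribution with df = n₁ + n₂ − 2 and noncentrality 1.5 × √(n₁n₂/(n₁ + n₂)), which is 1.5 × √(n/2) for equal groups. Reject when |t| exceeds the 97.5% point of t on df degrees of freedom.

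| Evaluable per group | df | Critical t | Noncentrality | Power |
|---|---|---|---|---|
| 7 | 12 | 2.179 | 2.806 | 73.1% |
| 8 | 14 | 2.145 | 3.000 | 79.7% (79.65%) |
| 9 | 16 | 2.120 | 3.182 | 84.8% |
| 10 | 18 | 2.101 | 3.354 | 88.7% |

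Simulation of the t-test with 20,000 trials per size gave 73.1%, 79.9%, 84.9% and 88.8%. The smallest equal group size with at least 80% power is 9. With 7 per group, 80% power needs an effect of 1.63 SD instead of 1.5.

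**4. The dropout reserve.** Implied by section 9: 10 − 7 = 3 per group. For the named test: 10 − 9 = 1 per group, or 10 − 8 = 2 if 79.65% is accepted as 80%.

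**5. Uneven losses from 10 + 10.**

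| Evaluable | Power |
|---|---|
| 9 and 10 | 86.8% |
| 8 and 10 | 84.3% |
| 8 and 9 | 82.2% |
| 7 and 10 | 81.2% |
| 7 and 9 | 79.0% |
| 7 and 8 | 76.4% |
| 7 and 7 | 73.1% |

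Within the allowance of three per group, power is clearly below 80% only when one group loses three and the other loses at least one. It reaches 73% only when both lose three.

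**The case against.** The strongest reply is that nothing was miscalculated: 7 is the standard normal-formula answer, the correct figure is only two patients away, and the trial enrols 10 per group, which gives 88.7%. Most of this stands. The fault is a missing small-sample correction, not a slip in arithmetic, and the enrolled number is sufficient. It does not save the sentence, because 73.1% is not 80% by rounding, and those two patients are two of the three treated as spare.

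It may also be said that 1 per group is too strict, since 8 per group falls short by only 0.35 points on an assumed effect size. That is fair, and the reserve is best given as 1 to 2. It is fair, too, that no dropout rate is stated. The 3 is inferred from 7 against 10.

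Matching and feasibility status are the context that section 9 offers for a small sample. An unpaired test makes no use of matching, and a paired calculation gives 6, so matching does not yield the 7. Feasibility status lowers the stakes but does not make a stated derivation correct.

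The Synopsis speaks of non-inferiority, which might suggest a one-sided test and so rescue the 7. Section 9 gives no margin and names a two-tailed test, and the aim in section 3 is to show a positive effect on oxygenation. The conflict over the hypothesis is a separate matter. The figures here apply to the analysis that section 9 specifies.

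Two stronger readings are tempting. The first is that the trial is underpowered. It is not at its planned size, nor when three patients are lost from one group alone. The second is that the Mann-Whitney branch makes matters much worse. Its simulated power at 7 per group is about 65% when the data are normal, but section 9 reserves that test for skewed data. Under assumed lognormal data with a 1.5 SD shift (log-SD 0.5, 0.8 and 1.0), simulated exact Mann-Whitney power at 7 per group is about 76%, 84% and 89%. The figure for normal data therefore does not describe that branch.

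**Conclusion.** The point holds as a moderate correction of a stated figure. For a 1.5 SD effect and a two-tailed unpaired t-test at 5%, 7 per group fall about 7 points short of the stated power (73.1% against 80%), and 9 per group are needed for at least 80%. The enrolled 10 per group are adequate, but the reserve is 1 to 2 per group rather than 3.

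This rests on four assumptions: 7 means per group; the two-tailed unpaired test in section 9 is the primary analysis; PaO2 is normally distributed with equal variance in the two groups; and the effect is 1.5 SD as stated. The protocol gives no basis for expecting three losses in each group, so 73% is what would remain after the full loss that section 9 implies it can absorb, not a forecast.

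**What to change.** Restate the calculation in section 9 along these lines:

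> Nine evaluable patients per group are needed for at least 80% power (84.8%) with a two-tailed unpaired t-test at the 5% level and an effect of 1.5 SD. Ten per group will be enrolled. This gives 88.7% power with no dropouts, 79.7% with 8 evaluable per group and 73.1% with 7.

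Replace the needed-to-treat wording with n per group, so that it is clear what the number counts. Keep the total of 20.

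The cost is one corrected passage and a slightly less favourable stated reserve. No patients are added and no procedure changes.

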## **10. Adverse Event Reporting**

Although we do not expect adverse events we will follow and report all adverse effects to ensure safety for the patients.

## **11. Ethical Consideration**

- The study will only be conducted after review and approval from MRC and ethical committee of IRB.
- All participating patients/or patient's family member will be asked for informed consent after explanation of the project and giving written information.
- There will be no change in treatment plan with the exception of the ventilation.
- We will maintain privacy for the subject throughout data collection by carrying out data collection in private rooms or areas that are partitioned.
- Data confidentiality will be maintained by the use of an individual study ID which is stored in a key file together with the identifier separately and safely. All collected data will be stored under the nominator of the study ID. All information is stored in a secured computer file in a locked office in HGH.

- All research is done under recognition of the Helsinki declaration and under full adherence to the MoPH regulations in Qatar.

## **12. Sponsor, Funding & Collaborator Information**

We rely on our own staff and devices HMC financial support for additional devices might be needed.

## **13. Dissemination of Results and Publication policy**

We are planning to present this study in local or international conference and published it in indexed journal (not decided) after completion of study.

## **15. Appendices**

- Poster Bergold (ref 7)
- Patient information and consent form
- Data collection sheet
- Delegate list
- Budget sheet
- SOFA-score table
